After the VE analysis had been conducted based on 110 cases, the study team planned discussions to review the findings and the value of continuing to enrol participants.

Two subsets of individuals, 1000 vaccinated individuals (500 adults and 500 children) and 500 pregnant participants (250 pregnant predose 1 and 250 pregnant within 30 days of dose 2), were enrolled for more active follow-up for safety reporting (table 3). The sample size allowed for 95% probability to detect at least one vaccine related serious adverse event (SAE) if the true incidence of that SAE is at least 1.2% with 250 individuals, 0.6% with 500 individuals, or 0.3% with 1000 individuals.

**Table 3 T3:** Time and event schedule for intervention delivery and safety evaluations

Preparation	Up to 1 month before study starts	D0 Dose 1 visit	D7 (−3/ +7 day)	D21 (−6/ +7 day)	D56 Dose 2 visit (−14/+28 day)	D7 post dose 2 (−3/ +7 day)	D21 post dose 2 (−3/+7 day)	1 month post dose 2 (−7 day/+1 month)	3 months post dose 2 (±14 day)	6 months post dose 2 (−14/+28 day)	3 months post delivery
Mapping and selection of study sites	X										
Community engagement and social mobilisation	X										
Consent, vaccination dose 1		X									
Vaccination dose 2					X*						
SAE assessment					X**†**			X‡			
Safety subset					X			X§			
All pregnant women					X**¶**			X			X**
Pregnancy subset		X	X††	X††	X	X††		X††	X††	X††	X‡‡
Immunogenicity subset					X§§		X§§				

*Dose 2 may be given between D42 and D84. Participants who return for dose 2 after 84 days will still be vaccinated.

†D56 safety data are collected at dose 2 visits.

‡Passive serious adverse event (SAE) recording from main study participants through participant-initiated phone calls or other contact with team, until 1 month post dose 2.

§Safety subset: 1000 participants will be actively followed up for SAEs by phone at 1 month post dose 2.

¶If study vaccinations have been paused, all pregnant participants who have not received dose 2 will be called at D56 (±7 days) to collect safety data.

**All pregnant women will have their birth outcomes collected around 3 months post delivery (between 1 and 3 months). When feasible, team to visit if the woman is not contactable by telephone.

††Pregnancy subset: safety telephone calls to collect SAEs at D7 and D21 post dose 1, and then at D7, 1 month, 3 months and 6 months post dose 2, unless delivery is before these time points.

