After the study start, all individuals presenting to an ETC, peripheral health facility or an EVD testing centre were expected to have their rVSV-ZEBOV-GP and Ad26.ZEBOV, MVA-BN-Filo vaccination status confirmed as part of routine data collection, with this information being recorded in the routine Ministry of Health EVD surveillance database. This included recording the participant identification (ID) number from the study vaccination card. If the patients were not able to present their cards at the ETC but mentioned being a study participant, ETC staff requested the family to bring the card to the ETC. For lost cards, we instructed ETC staff to collect the patient’s name, vaccination and clinic site details, and, if possible, the last vaccination date, and provide this information to the study data management team to retrieve the participant’s ID number and manually complete the ETC line-list.

Due to the waning EVD outbreak, the Trial Steering Committee decided to suspend dose 1 vaccination on 29 February 2020, after 20 427 participants had been vaccinated. Dose 2 vaccination continued, recognising that, while the objective of evaluating VE could no longer be met, the other objectives were still achievable. However, due to the COVID-19 outbreak in DRC, all study vaccinations were suspended from 10 April to14 September 2020, while special precautions to ensure the safety of participants and staff from COVID-19 were established. As a result of suspension of activities, the protocol was amended (10 August 2020, version 7.0) to include immunogenicity assessment of the impact of delayed dose 2 vaccination beyond 84 days post dose 1 and safety follow-up windows (table 3). Following implementation of infection control measures, vaccination continued and dose 2 delivery was completed on 9 February 2021.

In addition to the main study, we enrolled participants into three subsets, with consent sought in separate sections in the main study informed consent and assent forms (online supplemental appendixs 1–10):

10.1136/bmjopen-2021-055596.supp2Supplementary data

10.1136/bmjopen-2021-055596.supp3Supplementary data

10.1136/bmjopen-2021-055596.supp4Supplementary data

10.1136/bmjopen-2021-055596.supp1Supplementary data

10.1136/bmjopen-2021-055596.supp10Supplementary data

10.1136/bmjopen-2021-055596.supp9Supplementary data

10.1136/bmjopen-2021-055596.supp8Supplementary data

10.1136/bmjopen-2021-055596.supp7Supplementary data

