### Safety measurements

Following each vaccination, we gave participants instructions to contact the study team for any SAEs occurring up to 1 month post dose 2 and where to seek care for medical problems, including antenatal care for pregnant women (table 3). Whenever possible, we documented the diagnosis or syndrome related to SAEs, rather than multiple symptoms. Investigators then assessed any potential causal relationship to vaccination. We followed up SAEs to resolution or stabilisation, irrespective of severity or whether considered vaccine related. We allowed unscheduled study follow-up visits on adverse events at the investigator’s discretion.

Follow-up of pregnant women is ongoing. We compiled a registry of pregnant women and we encouraged women who become pregnant within 1 month of any vaccine dose to contact the team. We are telephoning all known pregnant women 1–3 months after delivery to record birth outcomes or, when possible, a study clinician visits them in person if they are not contactable by telephone. In the pregnancy subset, we actively follow by telephone 250 women who were pregnant at the time of dose 1 and up to 250 who became pregnant within 30 days (1 month) of administration of either dose 1 or 2. We make calls to collect SAE data at D7 (−3/+7 day) and D21 (−6/+7 day) post dose 1, D7 (−3/+7 day) post dose 2, and at 1 month (−7 day/+1 month), 3 months (±14 day) and 6 months (−14/+28 day) post dose 2 (unless delivery occurs before these time points). We are performing a clinical examination on the first 100 infants born to women in the pregnancy subset at around 3 months of age (ranging from 1 to 6 months). We offer a small bag of rice, cassava or equivalent to mothers returning to the clinic for infant safety follow-up visits.

In the safety subset, we actively followed the first 500 adults and first 500 children enrolled by telephone 1 month (−7 days/+1 month) after administration of dose 2.

For acute medical problems, we provide care to participants with referral to health clinic and hospitals as necessary. The trial sponsor and funder have put in place global and local clinical trial insurance covers to compensate any potential harm to participants.

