### Safety analysis

Safety analyses will include all participants receiving at least dose 1. We will summarise the incidence of SAEs overall, by time since vaccination and by age and whether or not vaccination was received during pregnancy. The incidence of SAEs will also be tabulated by MedDRA preferred term and system organ class (Medical Dictionary for Regulatory Activities version 23.1).

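### The SAE split by vaccination in pregnancy sets repeatedly telephoned women beside a mostly passively followed population, so recorded incidence is tilted upward in pregnancy even at equal true risk.

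*Protocol article*

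**What the plan says.** **Population and split.** The Safety analysis section sets the population: "Safety analyses will include all participants receiving at least dose 1". It then splits SAE incidence "by time since vaccination and by age and whether or not vaccination was received during pregnancy". Intervention delivery gives the number: dose 1 stopped "after 20 427 participants had been vaccinated".

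**Window.** Outcomes counts SAEs from first vaccination to 1 month after dose 2, and Table 1 gives the same timeframe for safety. The Safety analysis section does not repeat it.

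**How SAEs are found.**
- Pregnancy subset (up to 500 women): a Table 3 footnote schedules six SAE calls, two following the first dose and four following the second, the last of them at half a year. Each call applies "unless delivery is before these time points".
- Safety subset, Safety measurements: "we actively followed the first 500 adults and first 500 children enrolled by telephone", once, 1 month after dose 2.
- Everyone else, Table 3 footnote: "Passive serious adverse event (SAE) recording from main study participants through participant-initiated phone calls" (other routes to the team also count), plus SAE collection for those who attend the dose 2 visit.
- All pregnant women, Table 3: entries at the dose 2 visit and 1 month after dose 2. A footnote adds a day 56 call for pregnant participants still awaiting dose 2 if vaccination is paused.

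**The concern.** The stratifying variable is closely tied to how hard SAEs are looked for. Women vaccinated in pregnancy are the group with the most scheduled contacts. The group shown beside them is nearly everyone else, of both sexes and from 1 year of age, most of whom must contact the team themselves. Two incidences printed side by side will be compared, whether or not a test is planned.

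This matters because the article presents the trial as the first to give the regimen to pregnant women, and this split is the only SAE analysis by pregnancy that it states. An excess could come from detection alone and be taken as a safety signal. The absence of an excess would be weak reassurance, because the comparison group differs in age, sex and follow-up.

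**Working it through.** **1. The plan's own safety figure.** The Sample size section states a 95% chance of seeing at least one SAE at three true incidences. Using 1 − (1 − p)^n:
- n = 250, p = 1.2%: 0.9511
- n = 500, p = 0.6%: 0.9507
- n = 1000, p = 0.3%: 0.9504

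The figures reproduce. They concern absolute detection within a subset, not a contrast between groups.

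**2. Scheduled contacts inside the outcome window.**

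| Group | Calls to 1 month after dose 2 | Asked at dose 2 visit |
|---|---|---|
| Pregnancy subset (up to 500) | 4: days 7 and 21 after dose 1; day 7 and month 1 after dose 2 | yes |
| Safety subset (1000) | 1: month 1 after dose 2 | yes |
| Main study | 0 | yes, if they attend |

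The pregnancy-subset calls at 3 and 6 months fall outside the window.

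**3. Share of participants called.**
- Safety subset: 1000 / 20 427 = 4.9%.
- No planned SAE call under either subset: 20 427 − 1000 − 500 = 18 927, or 92.7%, assuming the subsets do not overlap.

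**4. Size under stated assumptions.** The document gives no detection probabilities. Assume equal true SAE rates, dose 2 at day 56, calls that find every SAE, equal capture before dose 2 (because attenders are asked at that visit), and self-report that finds a fraction p after dose 2. With about 5% of the comparison group called, capture after dose 2 on that side is 0.05 + 0.95p. Over the window of 56 + 30 = 86 days:

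ratio = 1 / [56/86 + (30/86)(0.05 + 0.95p)]

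- p = 0.6: 1 / [0.651 + 0.349 × 0.62] = 1.15
- p = 0.2: 1 / [0.651 + 0.349 × 0.24] = 1.36

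**5. How far the answer depends on those assumptions.** Equal capture before dose 2 favours the plan, because the calls at days 7 and 21 also find SAEs. If the dose 2 visit is ignored and one sensitivity applies to the whole window, the ratio is a / [f·a + (1 − f)·s]. Here a is capture by calls, s is capture by self-report, and f = 1000 / (20 427 − 250) = 0.050, taking 250 women as pregnant at dose 1. For a of 0.9 to 1.0 and s of 0.3 to 0.9, the result runs from 1.0 to 3.0. The direction is stable and the size is not.

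**The case against.** **No comparison is planned.** True: the split is descriptive, with no ratio or test, and the subsets were sized for absolute detection. That lowers the stakes. It does not make the two incidences comparable, and the section carries no caution.

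**The SAP may deal with it.** The article refers analysis populations and subgroup analyses to the SAP. That sentence stands under the immunogenicity heading but may be meant generally. The SAP could well fix window handling. The article itself, however, has already chosen all dose 1 recipients as the population and pregnancy as the split, and that stated choice is the point here.

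**Others are not wholly unasked.** This stands. Everyone who attends for dose 2 is asked about SAEs, which is why step 4 assumes equal capture before dose 2.

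**The subset is not the stratum.** This also stands in part. Up to 250 subset women conceived after a dose and may be counted as not vaccinated in pregnancy. That raises the called share of the comparison group only from 5.0% to 6.2% (1250 / 20 177). With full capture by calls and 50% by self-report, the step 5 ratio moves from 1.91 to 1.88.

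**A stronger reading to avoid.** A reader might infer a 2.8-fold inflation from follow-up time (56 + 183 = 239 days against 86). The documents do not support that as the expected bias. Outcomes and Table 1 cap SAEs at 1 month after dose 2, and calls stop at delivery. If gestation is taken as 280 days, a woman pregnant at dose 1 reaches day 239 undelivered only if vaccinated in about the first 41 days. Even without the cap, 100 to 140 days of follow-up would give 1.2 to 1.6. A reader might also take the post-dose-2 month alone, where p = 0.2 gives 1 / 0.24 = 4.2. That is one month of the window under the most extreme of the assumed values.

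**Conclusion.** The point holds as a matter of direction. Inside the plan's own SAE window, scheduled detection is heavier on the pregnancy side, so equal true risk yields a higher recorded incidence there, provided calls find at least some SAEs that self-report misses. The size cannot be derived from the document. The range of 1.15 to 1.36 rests on assumed sensitivities, an on-schedule dose 2 and equal capture before it. Dose 2 was delayed for some participants by the 2020 suspension, which changes the weighting by an unknown amount.

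The difference in age and sex between the two sides is a separate problem; its direction is not known from the document. Neither problem affects the overall SAE summary as a description of what was recorded. This is a correctable presentation choice that should be changed, not a flaw that invalidates the safety evaluation.

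**What to change.** In the Safety analysis section:
1. State that the pregnancy split uses the SAE window given in Outcomes.
2. Keep the all-participant summary, but tabulate it by follow-up mode: pregnancy subset, safety subset, passive.
3. Add one like-for-like table: actively followed women vaccinated in pregnancy against non-pregnant safety-subset women of the same age range, counting SAEs elicited at the contacts both have (dose 2 visit and 1-month call).
4. Report in separate rows the SAEs found only at the day 7 and day 21 calls, and those occurring later than 1 month after dose 2, so that nothing is lost from reporting.
5. State that the contrast with the whole passively followed population is not to be interpreted as an effect of vaccination in pregnancy.

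The cost is wording and a few table rows from data already being collected. The comparator becomes much smaller (the number of women among the 500 safety-subset adults is not stated), so intervals widen. Matching contacts does not remove SAEs that belong to pregnancy itself, such as obstetric admissions, and the report should say so.

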### Immunogenicity subset analysis

We will determine the number of overall participants with detectable antibodies and maximum titres post vaccination, including analysis by age group and by time since dose 1 vaccination. We will make descriptive comparisons with other studies of the same vaccine in sub-Saharan Africa where dose 2 was given according to the recommended 56-day interval and, for adults, with other delayed dose 2 immunogenicity data. We will analyse continuous immunological parameters (eg, geometric mean concentration of IgG binding antibodies to EBOV GP) and responder rates, and assess the impact of extending the interval between the two doses.

More detailed information on analysis populations, data handling and subgroup analyses is provided in the statistical analysis plan.

### Qualitative research analysis

We are conducting inductive and deductive analysis of qualitative data collected by in-depth interviews, focus group discussions and exit interviews. All recordings are being transcribed into French and imported to NVIVO V.12. Data are being coded by constant comparative methods to create emergent themes.

### Trial management

LSHTM is the study sponsor. A Trial Steering Committee holds regular meetings by teleconference to monitor study progress (online supplemental appendix 11). An independent Data Safety and Monitoring Board (DSMB) periodically reviews the safety data and meets according to the participant recruitment timeline specified in the DSMB Charter (online supplemental appendix 11). Fatal, life-threatening events and Suspected Unexpected Serious Adverse Reactions are reported to the DSMB within 48 hours and other SAEs within 7 days. An independent GCP monitor checks to compliance with the protocol, GCP, standard operating procedures and informed consent processes through review of documents for 5% of study participants through on-site visits and remote monitoring. There will also be one on-site GCP audit by a sponsor representative not involved in conducting the trial before primary data collection has completed. Please see online supplemental appendix 12 for the responsibilities of the study sponsor and funders.

10.1136/bmjopen-2021-055596.supp11Supplementary data

10.1136/bmjopen-2021-055596.supp12Supplementary data

## Ethics and dissemination

The protocol was reviewed and approved by the Comité National d’Ethique et de la Santé and Comité d'Ethique de l'Ecole de Santé Publique in DRC, the LSHTM Ethics Committee and the Ethics Review Board of MSF (table 1). This study is being implemented according to the Declaration of Helsinki principles and the principles of the International Conference on Harmonisation (ICH) Guideline for GCP. Since the original approved protocol version 5.0, dated 12 September 2019, there has been two protocol amendments. This article is based on protocol version 7.0, dated 10 August 2020. All versions and amendments have been approved by the four ethics committees listed above and by the DRC Direction de la Pharmacie et du Médicament. The study has been registered in ClinicalTrials.gov (ClinicalTrials.gov Identifier: NCT04152486).

The population of North Kivu Province is considered vulnerable. Study participation is strictly voluntary. Participants can withdraw from the trial at any time. If provided, the reasons for withdrawal will be recorded. Both communities and, at the time of the outbreak, individuals were informed that study participation did not mean that other EVD infection protection and control measures should be discarded and that they should endeavour to attend for the second dose.

Results of the study will be presented to relevant stakeholders in DRC, shared with WHO’s technical expert groups and published in open access journals. Any research articles generating from this trial will be subject to the Publication Policy and the Authorship Guidelines agreed by all partners.

### Patient and public involvement statement

Because we invited the general population to participate in this trial, no patients were involved in the discussions on trial design, conduct, reporting or dissemination. Prior to trial commencement, we engaged the Goma population through consultation with local authorities and leaders. Refer to the main article for details.
